#### Qualitative analysis approach

During qualitative interviews households’ feedback, impressions, comments on their experience and health impacts are gathered, as well as their understandings of why things worked well or did not work out for them. These insights provide explanatory findings for the project in general, and also allows study sites to modify their activities after the baseline stage to better target those that are excluded. An iterative approach to qualitative analysis of interview data is therefore undertaken, after each round of data collection. Interview data are digitally recorded, transcribed and translated for analysis, a process led by the lead qualitative partner and drawing on the experience and expertise of key collaborators from each study site. Analysis seeks explanations of site-specific phenomena, as well as attempting to generalise about experiences of energy poor households in the face of interventions across Europe.

### Dissemination

A comprehensive dissemination and communication strategy is designed and implemented. Scientific dissemination includes papers and proceedings submitted to international conferences or peer-reviewed journals. A scientific committee supports and monitors scientific dissemination. Authorship is determined in accordance with the ICMJE authorship guidelines. Dissemination aimed at local authorities, social workers, health professionals, energy providers and the civil society (associations and NGOs) is done through the project website (https://wellbased.eu), professional magazines, congresses, fairs and (capacity building) workshops organised within the project. Networks and alliances on health and/or poverty, vulnerability or climate change are strengthened to reinforce the impact of the dissemination activities.

## Discussion

### Summary of the study aim

This study aims to evaluate the potential benefits of the WELLBASED intervention programme on several indicators of health, wellbeing, and energy poverty. The programme offers a framework of actions targeted at individual lifestyle factors, social and community networks, living and working conditions and socio-economic and environmental conditions. A pre-post controlled design is used and the WELLBASED intervention programme is implemented in six European study sites: Valencia, Spain; Heerlen, The Netherlands; Leeds, United Kingdom; Edirne, Turkey; Obuda, Hungary, and Jelgava, Latvia.

Energy poverty is highly prevalent in Europe [1, 2]. Multiple studies showed the adverse effects of living in energy poverty conditions on human health and wellbeing [7–12]. This multidimensional problem faced by many European citizens calls for a comprehensive approach to alleviate the negative impact on their health and wellbeing. Moreover, climate mitigation targets under the Paris agreement are creating further pressure to reduce household energy consumption, and fund renewable energy or energy efficiency measures. The ways in which such measures are funded can have an important impact on energy poor households: if funds are levied through energy bills this has an inequitable impact on poorer households [43]. In any case, poorer households already find it difficult to afford adequate household energy. Wealth inequality is known to affect energy consumption, and people with low incomes already spend a higher proportion of their income on energy bills [44]. This leaves them unable to afford investments in renewable energy, [6] and at risk of further vulnerability from the energy transition.

### Strengths

This study has several strengths. WELLBASED aims to implement a comprehensive intervention to fight both energy poverty and its effects on health and wellbeing across Europe. The interdisciplinary approach to the evaluation method, and comprehensiveness of data collection are a unique opportunity, creating a rich and valuable dataset on the impacts of these interventions on energy poverty and health. The development of the WELLBASED urban programme is co-created with stakeholders and end-users to ensure it serves their needs. The implementation and evaluation of the programme in different countries provides information on the generalizability and feasibility of the approach in various European settings. By utilizing a uniform questionnaire and standardized measurements, a cohesive evaluation is applied. Analysis, conclusions and recommendations drawn from mixed methods data collection during the study are rooted in the social-ecological model. This enhances insights into the impacts of particular interventions on different people, as well as the comparison of interventions and outcomes across countries.

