### Power consideration

WELLBASED counts with a total sample size of 1750 participants (*n* = 875 intervention group and *n* = 875 control group) distributed among the six study sites, with a minimum of 125 participants per arm per study site, as shown in Table 1. A 20% loss to follow-up (e.g. due to mortality, rehousing or impossibility to participate, as reflected in for this type of long-term studies) is expected [40]. This means the sample consists of *n* = 700 in the intervention group and *n* = 700 in the control group (total *n* = 1400) at 18-month follow-up. Equal standard deviations in the intervention and the control group are assumed, with alpha of 0.05 and power of 0.80. Thus, given six study sites with each an intervention group and control group, applying a correction factor to account for the clustered design, assuming an average cluster size of 117 citizens (1400/12) and an intra-class correlation coefficient of 0.02. For this expected overall sample size and assumptions, with regards to the continuous outcome measures (in particular, HRQoL) a difference of 0.28 standard deviation (SD) between the intervention and the control group can be detected at follow-up. This means that both at the European level, and in addition in each study site separately, small differences regarding the outcomes in the intervention group compared to the control group can be shown.

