### Data management and analysis

Data from all study sites are pseudo anonymized and combined in an online data platform (handled by INCLIVA). Erasmus University Medical Center is responsible for analysis and reporting. As the project will collect health-related data, special attention is attributed to the role of each partner in terms of controllers and processors, and to the organizational and technical measures to be put in place to ensure General Data Protection Regulation (GDPR) compliance. In addition, the risks associated to data processing will be defined in the Data Protection Impact Assessment (art. 35 GDPR) to be evaluated together with the Controllers’ Data Protection Officers. The data management plan includes procedures for ensuring a high-quality data standard, according to the FAIR principles: Findability, Accessibility, Interoperability, and Reusability [41]. All data are handled confidentially and scientific data are stored anonymously.

Descriptive statistics are used to describe participant characteristics in each study site and in the total study population, and to describe implementation outcomes in the study sites. Differences between T0, T1, T2 and T3 measurements are evaluated using multilevel linear regression analyses for continuous outcome variables and multilevel logistic regression analyses for dichotomous outcome variables. Interaction tests are performed for age, gender, living situation and education level to evaluate effects in subgroups. Statistical analyses are repeated for each study site separately. We consider a *P*-value of 0.05 or lower to be statistically significant. Analyses are performed according to the ‘intention to treat’ principle. An additional per protocol analyses is performed to evaluate the impact of the dose of the intervention received on outcomes.

A preliminary cost-effectiveness analysis is performed with the baseline measurement as control condition from a healthcare perspective. The healthcare costs per individual participant are calculated by multiplying resource use (e.g., doctor appointments, hospital admissions) with corresponding unit prices if available. Utility values are calculated using the EuroQol 5-level EQ-5D (EQ-5D-5L) to estimate the quality-adjusted life years (QALYs) [27]. EQ-5D-5L has demonstrated good measurement properties such as ceiling effects, reliability, and sensitivity [42].

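### Comparison across countries is claimed as a strength, but the only between-arm site analysis stated is a separate repeat in each site at 0.05, which cannot show whether effects differ between sites

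*Protocol article*

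**What the plan says.** Three parts of the protocol article bear on this.

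- **Strengths (Discussion).** "The implementation and evaluation of the programme in different countries provides information on the generalizability and feasibility of the approach in various European settings". After describing conclusions drawn from mixed-methods data, the section adds that the approach helps in understanding impacts on different people, "as well as the comparison of interventions and outcomes across countries".
- **Data management and analysis.** Multilevel models are used, and then: "Interaction tests are performed for age, gender, living situation and education level to evaluate effects in subgroups. Statistical analyses are repeated for each study site", each on its own. The threshold is general: "We consider a *P*-value of 0.05 or lower to be statistically significant". Neither site nor country is among the four interaction factors.
- **Power consideration.** The calculation is made "with alpha of 0.05 and power of 0.80", "assuming an average cluster size of 117 citizens (1400/12) and an intra-class correlation coefficient of 0.02", and concludes that "a difference of 0.28 standard deviation (SD) between the intervention and the control group can be detected at follow-up". The section then says that small differences can be shown overall and also within each site on its own.

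**The concern.** Comparing countries is a question about differences between effects. Its null hypothesis is that the programme effect is the same in every site. A test run inside one site has another null: no effect there. Six such results side by side do not test the first null, and none of them estimates how far two sites differ.

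The protocol deals with this correctly for age, gender, living situation and education, where it names interaction tests. For site it states only separate repeats. With moderate power per site, some sites will reach 0.05 and others will not even if the programme works equally well everywhere. Which sites succeed depends on chance and partly on size (177 per arm in the largest site, 125 in the two smallest). The results are meant for local authorities in several countries, so a spurious pattern of success in one city and failure in another could affect decisions. The statement that each site alone can show small differences makes that reading more likely.

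**Working it through.** **Inputs.** From the protocol: alpha 0.05 (taken as two-sided), power 0.80, 700 per arm analysed, cluster size 117, ICC 0.02, planning difference 0.28 SD, 20% loss, and Table 1 sizes per arm of 177, 156, 125, 146, 125 and 146. Assumed: one identical true effect in all sites; a comparison of final values; no cluster effect within a site unless stated; baseline correlation r, which the protocol does not give.

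**1. The plan's own figure.** Design effect = 1 + (117 − 1) × 0.02 = 3.32. Detectable difference = (1.96 + 0.84) × √(2 × 3.32 / 700) = 0.273 SD. Power at 0.28 SD is 0.82. The stated 0.28 SD is reproduced and is slightly conservative.

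**2. One site alone.** After 20% loss, the number per arm is m = 141.6, 124.8, 100, 116.8, 100 and 116.8.

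- Detectable difference at 80% power = 2.80 × √(2/m): 0.33 SD in the largest site and 0.40 SD in the two smallest. No site has 80% power for 0.28 SD.
- If the ICC of 0.02 also applied within each site, the figures would be 0.65 to 0.68 SD.
- Power at 0.28 SD = Φ(0.28/√(2/m) − 1.96) = 0.65, 0.60, 0.51, 0.57, 0.51 and 0.57.

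**3. Chance of a mixed set of verdicts when all sites share one effect.** Mixed means at least one site significant in favour of the programme and at least one not. P(mixed) = 1 − Πp − Π(1 − p).

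At 0.28 SD: Πp = 0.033 and Π(1 − p) = 0.006, so P(mixed) = 0.961. On average 3.4 sites are significant and 2.6 are not. A simulation of 200,000 trials also gave 0.961.

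| Common effect (SD) | P(mixed), unadjusted |
|---|---|
| 0.10 | 0.52 |
| 0.15 | 0.75 |
| 0.20 | 0.91 |
| 0.28 | 0.96 |
| 0.35 | 0.81 |
| 0.40 | 0.60 |
| 0.50 | 0.20 |

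It is at least 0.90 only from about 0.20 to 0.315 SD.

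**4. Sensitivity.** Baseline adjustment multiplies the variance by 1 − r². At 0.28 SD, P(mixed) is 0.95 for r = 0.3, 0.89 for r = 0.5, 0.81 for r = 0.6 and 0.64 for r = 0.7. Adjustment does not always help: at a true 0.20 SD it raises P(mixed) from 0.91 to 0.96 for r = 0.5. With the ICC of 0.02 applied within sites and no adjustment, P(mixed) at 0.28 SD is 0.77.

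**5. What a site-by-arm test would do.** With an identical effect and no cluster effects, a 5-df heterogeneity test at 0.05 rejects in 5% of trials. The plan, however, assumes 12 clusters (1400/12), one for each arm in each site, so a cluster effect and a site-by-arm effect are the same contrast. In simulation, a test that ignores this rejects in 22% of trials at ICC 0.005, 40% at 0.01 and about 66% at 0.02. A closed form agrees: the critical value 11.07 divided by 3.32 is 3.33, and a chi-square on 5 df exceeds that with probability 0.65.

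**The case against.** A reader might infer that the plan intends to compare countries by counting which sites reach 0.05. The document does not say so. The sentence in Strengths concerns mixed-methods data, and the Objectives and Hypothesis sections pose no between-country hypothesis; differential impact there concerns gender and social determinants. The misreading is a foreseeable risk, not a stated plan.

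Nor are the separate tests the only work by site. Site descriptives, implementation outcomes and qualitative analysis of site-specific findings are also planned, and repeated regressions give estimates as well as P-values. The analysis plan is not shown and may contain a site-by-arm term, so its absence from the trial as a whole cannot be established.

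It would also be too strong to say that identical sites will almost always disagree. That depends on the true effect and on baseline adjustment, as the table and sensitivity results show. Since the main outcome is change in quality of life, the adjusted figures may lie nearer the actual analysis.

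Site-specific estimation is reasonable in itself, because the programme is adapted locally, target groups differ, and sites may allocate individuals or clusters. An interaction would mix all of these. The most serious objection is that a naive interaction test is not a clean remedy under the plan's own ICC.

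All of this stands as a limit on the point. What remains is that the protocol lists its interaction factors, leaves site out, gives site a method that cannot answer the cross-country question, and overstates what one site can show.

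**Conclusion.** The point holds in a limited form. The between-arm site analysis stated in the protocol cannot support the comparison of outcomes across countries that the article presents as a strength. At the trial's planning effect, a mixed set of site verdicts is the expected result of identical effects: about 96% unadjusted, and 64% to 89% if baseline correlation is between 0.7 and 0.5. These figures rest on Table 1 sizes less 20%, a two-sided 0.05 level, one common effect and, unless stated, no clustering within sites.

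The statement that small differences can be shown in each site does not fit the plan's own numbers if small means the 0.28 SD just quoted: one site needs 0.33 to 0.40 SD for 80% power, and more with clustering. This should be corrected before analysis, but it does not affect the pooled comparison of arms.

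**What to change.** In Data management and analysis, add wording such as: *Variation in the programme effect between sites is estimated in the pooled model with a site-by-arm term (fixed or random). Site-specific estimates with 95% intervals are shown together. Countries are not compared by whether the separate site analyses reach P of 0.05.*

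In Power consideration, replace the per-site sentence with the difference one site can detect at 80% power: 0.33 to 0.40 SD before any clustering.

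The cost is one model term and two sentences; no new data are needed. The limits should be stated beside the result. The term has limited power, so a non-significant result is not proof of equal effects. Where allocation is by group, the term cannot be separated from site-by-arm cluster effects (about 66% false signals from a naive test at the plan's ICC, not 5%), so a significant result is not proof that the programme effect differs. The estimates and intervals should therefore carry the comparison, not the test.

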### Limitations

We also expect to encounter some challenges. Participation of vulnerable people living in energy poverty may be challenging. The recruitment strategy seeks to involve societal partners that hold a trusting relationship with the target group. This has been shown to be an effective strategy in engaging hard-to-reach populations in health research [45, 46]. Furthermore, using the questionnaire we aim to capture the most important confounding variables to control for differences between participants in the intervention and control condition; however it remains possible that study results are subject to confounding.

## Data Availability

The datasets used during the study are available on reasonable request by contacting the corresponding author.

## Abbreviations

BMI: Body Mass Index
EPOV: Energy Poverty Observatory
EQ-5D-5L: 5-Level EQ-5D
FAIR: Findability, Accessibility, Interoperability, Reusability
GDPR: General Data Protection Regulation
HR-QoL: Health-related quality of life
IoT: Internet of Things
NGO: Non-governmental organization
QALYs: Quality-adjusted life years
RE-AIM: Reach, Effectiveness, Adoption, Implementation, Maintenance
SD: Standard deviation
SF-12: Short-form health survey 12
SpO_2_: Oxygen saturation
